### Statistical analyses and sample size

The following potentially confounding measures will be compared between the two intervention groups: CMSA, BBS, NIH-SS, ABC, and length of stay (in-patient rehabilitation). Measures that differ significantly between the two groups will be included as covariates in statistical models comparing interventions. Repeated-measures analysis of variance (ANOVA) or analysis of covariance (ANCOVA; as appropriate), with group-by-time interaction, will be used to evaluate the effect of the interventions on walking activity, spatio-temporal characteristics of walking, and SEQ. Separate ANOVAs will be used for each outcome measure. The ‘group’ term is the intervention group; the ‘time’ term is the assessment time point. The group-by-time interaction effect will reveal if there is a greater change over time in one group compared with the other. Separate analyses will be conducted to compare measures at the first three time points; i.e. discharge from in-patient will be compared to study enrolment, and discharge from out-patient will be compared to discharge from in-patient. One-way ANOVA or ANCOVA will be used to compare the CIQ and satisfaction between the two groups at discharge from rehabilitation and three months post-discharge from in-patient. The frequency of goal attainment between the two groups will be compared at discharge from both in-patient and out-patient rehabilitation; intent-to-treat analysis will be employed for this outcome for all participants initially randomized, including those who withdraw from the study [24,57]. Barriers to walking will be documented.

For sample size estimates, we used change in total walking duration from the initial assessment to discharge from in-patient rehabilitation (i.e. the first phase of the study) as our primary outcome of interest. In our pilot work, we observed an average increase in total daily walking activity of 20 minutes from the initial assessment to discharge in a group of stroke in-patients. We expect that an average increase in daily walking activity of 40 minutes in the feedback group would be clinically meaningful (i.e. 20 minutes more than expected with no feedback). The standard deviation for change in daily walking time was 23 minutes in our pilot work. Using a sample size formula for repeated measures ANOVA [58], an improvement of 20 minutes of walking more in the feedback group than the no feedback group, a standard deviation of 23 minutes, a probability of a Type I error of 0.05 and probability of Type II error of 0.1, 28 individuals per group will be required in the final analysis. In order to achieve a final sample of 56 (i.e. 28 per group) we will aim to recruit approximately 62 participants (i.e. assuming that approximately 10% of participants will withdraw from the study). Sample size and power estimates using an updated standard deviation will be reassessed after the first 12 participants have completed the first phase of the study, as per CONSORT recommendations [59,60].

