## Methods

### Design overview

This is a single-blind randomized controlled trial with the assessor being blinded to the group allocation (participants cannot be blinded to group allocation). Participants will be randomly assigned, using allocation concealment, to one of two groups: feedback or no feedback. The study will span three phases of rehabilitation and recovery post-stroke: in-patient rehabilitation, out-patient rehabilitation, and post-rehabilitation community reintegration. Outcome measures will be obtained at up to four time points (Figure 2): 1) upon entry into the study; 2) immediately prior to discharge from in-patient rehabilitation; 3) immediately prior to discharge from out-patient rehabilitation (for those admitted to out-patient rehabilitation at the institution); and 4) three months following discharge from rehabilitation. This study was approved by the University Health Network research ethics board (protocol number 11-027-DE).

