### Intervention

Participants will be recruited into the study when they are deemed to be ambulatory without supervision. Patients with stroke tend to be discharged from in-patient rehabilitation 2–4 weeks after they reach this status. Therefore, the length of the in-patient intervention phase will vary between participants but will be approximately 2–4 weeks long. Out-patient rehabilitation services are offered in three blocks of 4–6 weeks duration; the first block is 6-weeks long to allow extra time for assessment prior to prescription of rehabilitation services. Participants in this study will be followed only for the first and second (if applicable) block of out-patient rehabilitation. The third block is often either not completed at all or not completed immediately subsequent to the second block (i.e. there may be a gap of a number of months between the second and third block). Therefore, the duration of the out-patient phase of the intervention is 6–10 weeks.

In order to ensure that all physiotherapists administer the intervention in a consistent manner, we will host a series of in-services concerning goal-planning of walking activity. These in-services will focus specifically on the output from the ABLE system, which is the new component of this study. Physiotherapists will learn how to interpret the output from the ABLE system and how to use this information to evaluate a patient’s progress towards their goals. Specific cases will be discussed based on pilot testing of ambulatory monitoring.

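### Covariates are chosen by testing for significant differences between the randomised groups, and the candidates include total in-patient length of stay, which is completed only after randomisation

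*Protocol article*

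**What the plan says.** The Design overview describes a randomised comparison: "Participants will be randomly assigned, using allocation concealment, to one of two groups: feedback or no feedback". Group allocation and blinding adds stratification by self-selected walking speed (below 0.42 m/s, or 0.42 m/s and above) in blocks of four.

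Statistical analyses and sample size names five measures as possible confounders: CMSA, BBS, NIH-SS, ABC and in-patient length of stay. These are compared between the groups, and the rule is: "Measures that differ significantly between the two groups will be included as covariates in statistical models comparing interventions". The main models are repeated-measures ANOVA or ANCOVA, read through the group-by-time interaction.

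The Intervention section fixes when stay becomes known. Enrolment happens during the stay: "Participants will be recruited into the study when they are deemed to be ambulatory without supervision". Discharge comes later: "Patients with stroke tend to be discharged from in-patient rehabilitation 2–4 weeks after they reach this status". The interval is not fixed: "the length of the in-patient intervention phase will vary between participants". Over that interval, the subsection on the in-patient phase gives physiotherapists of feedback participants a daily activity report, which they use to check adherence and to set harder sub-goals.

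**The concern.** Two different problems sit in one sentence.

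**The screen.** After proper randomisation, any difference between the groups on a measure taken at enrolment is due to chance. A significance test of that difference says nothing about whether the measure predicts walking outcome, which is the reason to adjust for it. The rule lets chance decide the final model, and it omits prognostic measures whenever they happen to be balanced. Walking speed, the one factor thought predictive enough to stratify on, is not on the list.

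**Length of stay.** Total stay ends at discharge, which is also when the outcome used for the sample size is measured. It may itself be a consequence of allocation. The rule admits it only when the arms differ on it, which is most likely when feedback has altered it. Adjusting then either removes part of the effect of interest or conditions on a variable that treatment and prognosis both influence.

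At stake is the estimate for the walking outcomes, because the rule applies to the models that compare the interventions.

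**Working it through.** **1. The plan's own figure.** Inputs from Statistical analyses and sample size: difference 20 min, SD of change 23 min, type I error 0.05 (two-sided reproduces the result), type II error 0.1.

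n per group = 2 × (1.960 + 1.282)² × 23² / 20² = 27.8, so 28. The stated 28 per group is reproduced, and nothing below changes it.

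**2. How often the screen selects something by chance.** Assumptions: independent tests, each at 0.05 (the article gives no level for the screen), and no true difference.

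- Five measures: 1 − 0.95⁵ = 22.6%.
- The four clinical scales alone: 1 − 0.95⁴ = 18.5%.
- The four scales with an assumed mutual correlation of 0.5: about 14–17% in simulation.

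**3. What the screen does for the four scales.** Simulated change scores, 28 per arm, SD 23, four scales correlated 0.5, 3,000 runs per setting. The share of outcome variance that the scales explain (R²) is assumed.

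| Assumed R² | Power at 20 min, screened | Power at 20 min, prespecified | Type I error, screened | Type I error, prespecified |
|---|---|---|---|---|
| 0.10 | 0.90 | 0.90 | 0.037 | 0.045 |
| 0.25 | 0.90 | 0.94 | 0.041 | 0.050 |
| 0.40 | 0.92 | 0.98 | 0.033 | 0.049 |

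Without any adjustment, power was about 0.89–0.90. The screen stays close to that, while prespecified adjustment gains power when the scales are moderately prognostic. Type I error is not inflated.

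**4. When a covariate reaches the group-by-time contrast.** With two time points and complete data, that contrast is the between-arm difference in mean change. A covariate that is constant over time and enters as a main effect cancels out of each person's change, so it leaves the contrast alone. If it is crossed with time, or used in an ANCOVA of the change, then:

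adjusted effect = unadjusted effect − b × (difference in mean stay between arms),

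where b is the within-arm slope of change on stay. The article does not say which form is meant.

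**5. Length of stay, in the form where it acts.** Write s for the shift in stay due to feedback, in within-arm SDs, and ρ for the within-arm correlation of stay with change in walking time. If stay is always adjusted for, the bias is −ρ × 23 × s minutes. The article gives neither s nor ρ, so these values are illustrations:

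- s = −0.5, ρ = ±0.3: ±3.45 min. ρ = ±0.5: ±5.75 min.
- s = −0.8, ρ = ±0.3: ±5.52 min. ρ = ±0.5: ±9.2 min.
- s = 0: no bias.

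Under the planned rule, stay enters only when significant. Simulated for that rule, with a true total effect of 20 min:

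| Assumed shift | Stay selected | Mean estimate, ρ = −0.3 to −0.5 | Mean estimate, ρ = +0.3 to +0.5 | Rejection rate if no effect on walking |
|---|---|---|---|---|
| 0.5 SD | about 45% | 17.8 to 16.2 | 22.3 to 23.7 | 0.06–0.10 |
| 0.8 SD | about 83% | 14.8 to 11.6 | 25.1 to 28.2 | 0.11–0.30 |

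**The case against.** The best defence is that the harm from length of stay is conditional. Nothing in the article says that feedback changes discharge timing, and both arms use the same action plans, coping strategies and goal re-evaluation. If feedback does not shift stay, there is no bias. Part of the stay also precedes enrolment and would be a legitimate baseline variable, and the form of the ANCOVA may be settled in an analysis plan that is not shown. All of this stands, and it limits the claim to possible bias. It does not rescue the rule, which names the whole in-patient stay and is stated outright.

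A reader might infer more than the article supports in three ways:

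- **A bias in minutes.** It is tempting to divide the 20-minute pilot gain by a 2–4 week phase and multiply by an assumed change in stay. The article gives no pilot duration. A mean gain per day is also not the slope of gain on stay across patients, which could be zero, or negative if slower recoverers stay longer.
- **Inflated false positives from screening the four scales.** Step 3 shows none.
- **An adjustment that is both inert and biasing.** These belong to different models: inert with a main effect only, active with a covariate-by-time term.

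**Conclusion.** The point holds as a fault in a stated rule.

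For CMSA, BBS, NIH-SS and ABC at enrolment, the cost is a data-dependent model and most of the available precision gain. How much precision is lost depends on how prognostic the scales are, which is assumed here. The figure of about 23% for chance selection is an upper guide that rests on five independent tests at 0.05.

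For total length of stay, the risk is bias of either sign. It requires that feedback alters discharge timing, that stay is related to change in walking, and that the covariate enters in a form that reaches the group-by-time contrast. The direction and size cannot be derived from the article; the tabulated shifts show what such bias could look like and do not predict it.

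**What to change.** - Delete the between-group significance screen.
- Remove total in-patient length of stay from the covariates and report it by arm descriptively.
- Prespecify baseline covariates whatever the observed imbalance. Use the walking-speed randomisation stratum in all models. For outcomes measured at enrolment (walking activity, spatio-temporal measures, SEQ), add the enrolment value in an ANCOVA of the later value.
- If the repeated-measures model is kept, enter covariates with a covariate-by-time term so that they act on the group-by-time contrast. Enrolment is then already a level of time and should not be used again as a covariate.
- Do not require an enrolment value for community integration, satisfaction or goal attainment, because Table 1 collects none.

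The cost is a short rewrite of the analysis paragraph and a choice between the two model forms. No new data are needed, and the sample size stays at 28 per group.

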**Methods:**

Participants will be randomly assigned to one of two groups: feedback or no feedback. Participants will wear accelerometers daily during in- and out-patient rehabilitation and, for participants in the feedback group, the participants’ treating physiotherapist will receive regular reports of walking activity. The primary outcome measures are the amount of daily walking completed, as measured using the accelerometers, and spatio-temporal characteristics of walking (e.g. walking speed). We will also examine goal attainment, satisfaction with progress towards goals, stroke self-efficacy, and community-integration.

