### Group allocation and blinding

Participants will be assigned using a blocked stratified randomization approach to one of two groups: 1) feedback of walking activity; or 2) no feedback of walking activity (i.e. control group). There will be two strata based on the factor walking speed. Walking speed predicts the level of community ambulation achieved following discharge from rehabilitation [5]. A threshold walking speed of 0.42 m/s has been found to be predictive of community ambulation post-stroke [32]; therefore, participants will be stratified according to self-selected walking speed (slow walkers: <0.42 m/s; moderate-fast walkers: ≥0.42 m/s). Stratification will help to ensure that the two groups do not differ significantly on this factor [33,34] and that there will be approximately equal numbers of participants assigned to each group. The block size within strata will be four participants.

Group allocation will be performed by the principal investigator. A computer-generated random sequence will be used to assign participants. The treating physiotherapists will administer the goal-setting/planning (including feedback, if appropriate). A blinded research assistant will conduct the assessments and process data. Participants cannot be blinded to group allocation and will be informed of the chance of being allocated to one of two groups.

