#### Primary outcomes – daily walking activity & control of walking

The primary outcome measures pertain to walking activity as averaged over three days around the first two assessment time points (i.e. enrolment into the study and discharge from in-patient rehabilitation), and over seven days before the last assessment time point (discharge from out-patient rehabilitation). A longer monitoring period will be used for the out-patient phase as patients have more options for mobility post-discharge. Summary, whole day, outcome measures will be used in the analysis; i.e. total walking duration, total number of steps taken and total distance walked. However, it is most relevant to community ambulation and aerobic fitness to show increased duration of continuous walking [46,47]; therefore, we will also calculate the frequency and duration of longer walking bouts (i.e. >5 minutes continuously). Furthermore, intensity of walking is also important for cardiovascular benefit; therefore we will determine the frequency and duration of ‘high intensity’ walking, defined by either a walking speed or cadence ≥ 85% of maximum walking velocity.

Increased walking practice should improve control of walking. Spatio-temporal features of self-selected walking will be measured using a 4 m-long pressure sensitive mat (GAITRite, CIR Systems, Inc, Havertown, Pennsylvania, USA). Participants will start walking at least 1 m away from the mat and will be instructed to walk across the mat until they reach a mark 1 m from the end of the mat. Participants will be instructed to walk at their normal pace. Participants will complete three passes across the mat and measures will be averaged across the three passes. Walking speed, cadence, step length, and symmetry of spatio-temporal measures [48] will be calculated. While it is possible to determine these measures from the daily walking activity collected using the ABLE system, standardized assessment is required for pre- to post-intervention comparison of spatio-temporal measures.

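### The protocol names at least 11 primary walking and gait measures, tested in two phases, but its 5% error rate and 90% power apply to only one of those comparisons

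*Protocol article*

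**What the plan says.** Three parts of the protocol article bear on this.

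- **Which outcomes are primary.** The abstract (Methods) uses the plural: "The primary outcome measures are the amount of daily walking completed, as measured using the accelerometers, and spatio-temporal characteristics of walking". The section on primary outcomes starts with whole-day summaries, "total walking duration, total number of steps taken and total distance walked". It then adds the frequency and duration of bouts longer than 5 minutes, the frequency and duration of high-intensity walking, and four gait-mat measures: speed, cadence, step length and symmetry.
- **How they are tested.** Under Statistical analyses and sample size: "Separate ANOVAs will be used for each outcome measure". The test is the group-by-time interaction. Enrolment versus in-patient discharge and in-patient versus out-patient discharge are separate analyses.
- **What the trial is sized on.** The same section takes one measure in one phase, the change in total walking duration from the initial assessment to in-patient discharge. It calls this, in the singular, the primary outcome of interest, but in a sentence about sample size estimates. The error rates appear only there: "a probability of a Type I error of 0.05 and probability of Type II error of 0.1".

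**The concern.** These statements do not fit together. Where the outcomes are defined, a whole family is primary and each member has its own test in each phase. Where the trial is sized, there is one primary comparison. Nothing in the article says that this comparison decides the trial. The primary-outcomes section even points elsewhere, since it describes longer continuous walking as most relevant to community ambulation and fitness, and that is not the measure used for sizing.

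At stake is how a result can be read. If total walking duration shows no difference but step length in the out-patient phase does, the outcome definitions allow that to be reported as a positive primary result. The 5% error rate in the sample size would not describe the risk of that claim being false.

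**Working it through.** **Inputs from the protocol article.** Difference: "an improvement of 20 minutes of walking more in the feedback group than the no feedback group". Standard deviation of change: "The standard deviation for change in daily walking time was 23 minutes in our pilot work". Errors: 0.05 and 0.1. Allocation: "there will be approximately equal numbers of participants assigned to each group". Withdrawal: about 10%. Sidedness is not stated.

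**Step 1: reproduce the stated size.** n per group = 2 × [SD × (z₁₋α/₂ + z₁₋β) / difference]² = 2 × [23 × (1.960 + 1.282) / 20]² = 27.8, so 28. This matches. A one-sided 0.05 gives 23 and does not, so the calculation is for a single two-sided test. For withdrawal, 56 / 0.9 = 62.2, which fits the stated approximate 62.

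Power at 28 per group: the standard error is 23 × √(2/28) = 6.147, and 20 / 6.147 = 3.254. Power = Φ(3.254 − 1.960) = 90.2% (89.2% with the t distribution). The size is right for the comparison it covers.

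**Step 2: count the primary tests.** Duration, steps and distance (3); long bouts, frequency and duration (2); high-intensity walking, frequency and duration (2); speed, cadence, step length and symmetry (4). The total is 11. Over two phases, 11 × 2 = 22. The count rises if several symmetry measures, or both the speed and cadence definitions of high intensity, are used. It falls if distance cannot be validated, which the section on the ABLE system leaves open.

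**Step 3: error rate if each test is judged at two-sided 0.05.** For m independent tests, P(at least one false positive) = 1 − 0.95^m in either direction and 1 − 0.975^m in favour of feedback.

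- 11 tests: 43.1% and 24.3%.
- 22 tests: 67.6% and 42.7%.

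The measures are not independent, and the documents give no correlations. For 22 test statistics with a common assumed correlation:

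| Assumed correlation | Either direction | In favour of feedback |
|---|---|---|
| 0 | 68% | 43% |
| 0.3 | 57% | 30% |
| 0.5 | 44% | 22% |
| 0.7 | 30% | 15% |
| 0.9 | 16% | 8% |

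The nominal values are 5% and 2.5%. If the two phases are instead taken as uncorrelated, or correlated at −0.5 because they share the in-patient discharge value, the figures at 0.9 become 23–25% and about 13%. At 0.5 they become 49–52% and 28–30%.

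Counting only the six measures named in the hypotheses at the end of the Background gives 12 tests. If independent, the figures are 46.0% and 26.2%.

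**Step 4: power if the family were corrected instead.** With Bonferroni and the same standardised effect (20/23) assumed for every measure:

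- 11 tests: α = 0.05/11 = 0.00455, z = 2.838. Power at 28 per group = Φ(3.254 − 2.838) = 66%. For 90% power, 45 per group are needed, or 90/0.9 = 100 recruited.
- 22 tests: α = 0.05/22 = 0.00227, z = 3.052. Power at 28 per group = Φ(3.254 − 3.052) = 58%. For 90% power, 50 per group are needed, or 100/0.9 = 111.1, so 112 recruited.

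Uncorrected, the family does not have the stated error rate. Corrected in this way, it does not have the stated power.

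**The case against.** The strongest reply is that a multiplicity rule is commonly left to the analysis plan, which is not shown, and that this article is condensed. That stands: the lack of a stated correction is not an error here. It does not remove the conflict, because which outcome is primary is a protocol decision and this article states it in two ways. A correction placed in the analysis plan would also leave 28 per group short of 90% power (Step 4).

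A reader might draw three stronger conclusions that the document does not support.

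- **That a positive trial is likely by chance.** The figures above 50% count results in either direction and need low correlation between the tests. The hypotheses are directional, and in favour of feedback no scenario reaches 50%. Duration, steps and distance describe the same walking, so independence is a poor central assumption.
- **That the protocol tests each measure at 5%.** The value 0.05 appears only in the sample-size calculation. Applying it to each ANOVA is an inference.
- **That the sized measure has no special standing.** It is called the primary outcome of interest, in the singular. That standing is limited, since it is given for sizing only and the article does not say that this measure alone decides the trial.

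**Conclusion.** Wrong as written: the article contradicts itself on what is primary. The stated 5% error and 90% power are correct for one comparison, the change in total walking duration from enrolment to in-patient discharge. They do not apply to the primary family of at least 11 measures in two phases.

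If each of 22 tests were judged at two-sided 0.05, the false-positive risk would be substantially inflated: about 16% to 68% in either direction and 8% to 43% in favour of feedback. These ranges rest on assumed common correlations from 0.9 to 0 and on the inferred per-test threshold. The power figures of 66% and 58% rest on Bonferroni and on equal standardised effects. The contradiction itself rests on none of these assumptions.

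**What to change.** State in the abstract, the primary-outcomes section and the analysis section that the change in total daily walking duration from enrolment to in-patient discharge is the single primary outcome, tested at two-sided 0.05. Make the other walking and gait measures, and the out-patient phase comparison, secondary. Report these as estimates with confidence intervals, or with a stated adjustment such as Holm. Settle this before any between-group comparison is seen.

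This follows the choice already made for the sample size, so 28 per group and 90% power stand. The cost is wording, plus the loss of primary status for the other measures. No new data or patients are needed. A stated multiplicity procedure over a primary family would also resolve the conflict, but the trial would then have to be resized; Step 4 shows the scale under Bonferroni.

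### Walking, gait and SEQ outcomes are compared as raw change scores, without the enrolment value or the walking-speed stratum as covariates: a valid first-phase test, but one that can give away precision at no saving

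*Protocol article*

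**What the plan says.** Under Statistical analyses and sample size, walking activity, spatio-temporal gait measures and SEQ are each analysed by repeated-measures ANOVA, or ANCOVA as appropriate. The treatment effect is read from the interaction: "The group-by-time interaction effect will reveal if there is a greater change over time in one group compared with the other". The analyses are run in pairs of time points: enrolment against in-patient discharge, then in-patient discharge against out-patient discharge.

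Five possible covariates are named (CMSA, BBS, NIH-SS, ABC and in-patient length of stay). Each enters only if the groups differ significantly on it. The enrolment value of the outcome is not among them; it appears only as the first level of the time factor.

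Under Group allocation and blinding, "participants will be stratified according to self-selected walking speed", with a cut at 0.42 m/s and blocks of four. No model in the analysis section has a term for this stratum.

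The sample size rests on "an improvement of 20 minutes of walking more in the feedback group than the no feedback group". Its variability input is an SD of change: "The standard deviation for change in daily walking time was 23 minutes in our pilot work". The error rates are "a probability of a Type I error of 0.05 and probability of Type II error of 0.1", and the result is "28 individuals per group will be required in the final analysis".

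**The concern.** With two time points, the interaction test is the two-sample t-test on change from the earlier value. That fixes the slope of the later value on the earlier one at 1. ANCOVA estimates the slope from the data, so it uses the enrolment measurement at least as well, and usually better. Enrolment walking is already scheduled for every participant, and walking speed must be known before a participant can be randomised. The adjustment therefore needs no new data.

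The provision for ANCOVA does not supply this adjustment. It covers only the five listed measures, and only those that happen to differ between groups.

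The stratum raises a separate, smaller matter. Balancing the groups on a prognostic factor and then leaving it out of the model tends to make the standard error slightly too large. In a trial of 56 analysed participants, what is at stake is interval width and power, not bias in the first-phase comparison.

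**Working it through.** **Inputs from the article.** Difference 20 min; SD of change 23 min; alpha 0.05 (taken as two-sided, because one-sided would give 23 per group, not 28); power 0.90; 28 per group; 1:1 allocation.

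**Inputs assumed, because the article gives neither.** The enrolment-discharge correlation rho, and the ratio lambda = SD at discharge / SD at enrolment.

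**Step 1: the plan's own figure.** n per group = 2 × (1.960 + 1.282)² × 23² / 20² = 27.8, rounded up to 28. So 28 is the sample size for a change-score comparison. Power at 28 per group is 90.2% by the normal approximation and 89.2% by the exact t-test. The 95% interval half-width is 1.96 × 23 × √(2/28) = 12.0 min.

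**Step 2: variance of ANCOVA relative to the change score.**
- Change-score variance is proportional to 1 + lambda² − 2·rho·lambda.
- ANCOVA residual variance is proportional to lambda²(1 − rho²).
- Their ratio is f = lambda²(1 − rho²) / (1 + lambda² − 2·rho·lambda). With equal SDs, f = (1 + rho)/2.
- f never exceeds 1, and equals 1 where rho × lambda = 1.

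**Step 3: results at 28 per group**, change SD held at 23, ANCOVA residual SD = 23·√f, exact t power with one degree of freedom spent on the covariate.

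| lambda | rho | f | Interval narrower by | Power |
|---|---|---|---|---|
| planned change score | – | 1 | – | 89.2% |
| 1 | 0.5 | 0.750 | 13.4% | 95.8% |
| 1 | 0.7 | 0.850 | 7.8% | 93.4% |
| 1.25 | 0.5 | 0.893 | 5.5% | 92.2% |
| 1.25 | 0.7 | 0.981 | 1.0% | 89.7% |
| 1.5 | 0.5 | 0.964 | 1.8% | 90.2% |
| 1.5 | 0.7 | 0.998 | 0.1% | 89.2% |

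Outside that range of rho, with equal SDs, power is 97.7% at rho 0.3 and 92.0% at rho 0.8. At lambda 1.25 and rho 0.8 the product is 1 and the gain is nil.

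**Step 4: simulation** of 56 participants, equal SDs, stratified blocks of four, 5,000 runs per setting. The stratum was a split on a noisy version of enrolment walking.

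| rho | Power: change score | Power: ANCOVA on enrolment value | Power: ANCOVA plus stratum | Type I error: change score |
|---|---|---|---|---|
| 0.3 | 90.5% | 97.8% | 97.7% | 3.7% |
| 0.5 | 89.7% | 95.4% | 95.3% | 4.0% |
| 0.7 | 90.1% | 93.5% | 93.3% | 4.3% |
| 0.8 | 89.9% | 91.7% | 91.5% | 5.0% |

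Type I error of the two adjusted models lay between 4.7% and 5.8%. Simulation error at a true 5% is √(0.05 × 0.95 / 5,000) = 0.3 percentage points. The unadjusted test is thus mildly conservative at the lower correlations. The gain comes from the enrolment value; the stratum adds nothing visible once that is in the model. In this simulation speed carried no information beyond enrolment walking, so the result does not exclude some gain if it does.

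**Step 5: chance imbalance.** At rho 0.5 with equal SDs, a change SD of 23 implies a raw SD of 23/√(2 × 0.5) = 23 min. One standard error of the enrolment difference is 23 × √(2/28) = 6.1 min. The change score over-corrects by (1 − 0.5) × 6.1 = 3.1 min, against a target of 20 min.

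**The case against.** The strongest reply is that nothing here is an error. Under randomisation the enrolment-to-discharge change-score test is unbiased, the trial is sized on the SD of change, and 28 per group reproduces. Design and analysis agree, and the planned power of about 90% is delivered. This stands.

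Second, the size of the gain depends on quantities that the article does not give. A reader might infer that the change score loses precision whenever the correlation is below 1. That is true only with equal SDs at both times. Walking time is expected to rise by 20 to 40 min a day, so a growing spread is plausible, though not documented, and the gain can then shrink to nothing. This also stands, and is why the size is given as a range.

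Third, a reader might expect the stratum term to bring a further gain in power. The simulation shows none once the enrolment value is included. A stratum term is also the kind of detail that an article may leave to a fuller document. What remains is that the covariates which the article does list omit the stratum.

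Fourth, it would be too strong to say that the estimate is left open to baseline imbalance. A change score subtracts the starting value, so only the over-correction in Step 5 remains, and stratifying on walking speed limits that further.

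Finally, for out-patient discharge the remedy alters the question, because the plan asks about change since in-patient discharge. This stands and must be stated openly.

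**Conclusion.** The point holds as a recommendation on efficiency. The article fixes a change-score test that uses neither the enrolment value as covariate nor the randomisation stratum, and its ANCOVA provision does not alter that. Apart from one degree of freedom, the planned test cannot be more precise than ANCOVA on the enrolment value, and it may be less precise.

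For an assumed rho of 0.5 to 0.7 the loss in interval width is 8 to 13% if the SDs are equal, 1 to 5.5% if the discharge SD is 1.25 times the enrolment SD, and about 0 to 2% at 1.5 times. Which of these applies cannot be settled from the article.

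A reader might infer that the trial is underpowered, that 28 per group is wrong or that the first-phase result would be biased. The documents support none of these. The stratum belongs in the model so that the analysis matches the randomisation and the mild conservatism of the standard error is removed, not for a material further gain in power.

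**What to change.** **Enrolment to in-patient discharge.** For each walking, gait and SEQ outcome, analyse the discharge value by ANCOVA with group, the enrolment value of the same outcome and the walking-speed stratum, all named in advance and kept whatever the observed group differences. SEQ stays a secondary outcome. Keep 28 per group, which then becomes a conservative size.

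**Out-patient discharge.** Use the enrolment value as covariate. The in-patient discharge value is measured after randomisation and may already carry an effect of the feedback. State that this analysis estimates the group difference since randomisation, not the change since in-patient discharge.

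**Cost.** The first-phase change is one sentence in the analysis section and needs no extra data. The out-patient change needs a further sentence and a deliberate decision, because it replaces the question that the plan now asks.
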